## Abstract

**Background:**

An abundance of literature is dedicated to research for the treatment of Attention Deficit Hyperactivity Disorder (ADHD). Most, is in the area of pharmacological therapies with less emphasis in psychotherapy and psychosocial interventions and even less in the area of complementary and alternative medicine (CAM).

The use of CAM has increased over the years, especially for developmental and behavioral disorders, such as ADHD. 60–65% of parents with children with ADHD have used CAM. Medical evidence supports a multidisciplinary approach (i.e. pharmacological and psychosocial) for the best clinical outcomes. The Neuro Emotional Technique (NET), a branch of Chiropractic, was designed to address the biopsychosocial aspects of acute and chronic conditions including non-musculoskeletal conditions. Anecdotally, it has been suggested that ADHD may be managed effectively by NET.

**Design/methods:**

A placebo controlled, double blind randomised clinical trial was designed to assess the effectiveness of NET on a cohort of children with medically diagnosed ADHD.

Children aged 5–12 years who met the inclusion criteria were randomised to one of three groups. The control group continued on their existing medical regimen and the intervention and placebo groups had the addition of the NET and sham NET protocols added to their regimen respectively. These two groups attended a clinical facility twice a week for the first month and then once a month for six months.

The Conners' Parent and Teacher Rating Scales (CRS) were used at the start of the study to establish baseline data and then in one month and in seven months time, at the conclusion of the study. The primary outcome measures chosen were the Conners' ADHD Index and Conners' Global Index. The secondary outcome measures chosen were the DSM-IV: Inattentive, the DSM-IV:Hyperactive-Impulsive, and the DSM-IV:Total subscales from the Conners' Rating Scales, monitoring changes in inattention, hyperactivity and impulsivity.

Calculations for the sample size were set with a significance level of 0.05 and the power of 80%, yielding a sample size of 93.

**Discussion:**

The present study should provide information as to whether the addition of NET to an existing medical regimen can improve outcomes for children with ADHD.

**Trial registration:**

Australian New Zealand Clinical Trial Registration Number: ANZCTRN 012606000332527

## Background

There is an abundance of literature dedicated to research for the treatment of Attention Deficit Hyperactivity Disorder (ADHD) [1-5]. Most of this research is in the area of pharmacological therapies with less emphasis in psychotherapy and psychosocial interventions [6-8] and even less in the area of complementary and alternative medicine (CAM) [9,10].

The use of CAM therapies, has increased over the years, especially for the developmental and behavioral disorders, such as ADHD[9,11-14]. Approximately 60–65% of parents with children diagnosed with ADHD have used CAM therapies [9,11,13,15,16]. Despite varied definitions of what constitutes a CAM therapy, most definitions of CAM include chiropractic. Whilst there is a great deal of research on spinal manipulation performed by chiropractors, there are very few studies to substantiate  the effect chiropractic treatment has on children with ADHD [17,18]. Most published articles are of case studies [19-21] case series [18,22,23] and small cohort studies with sample sizes ranging up to N = 7 [24,25]. Of these, only three are from peer-reviewed journals [19,20,24] regardless, all of these provide a low level of evidence without the follow-up of randomised controlled trials (RCT) to substantiate findings.

Medical evidence supports a multidisciplinary approach (i.e. pharmacological and psychosocial) for children and adolescents diagnosed with ADHD for the best clinical outcomes [1,3,7,8,26-32]. In fact, certain studies have shown that the multidisciplinary approach produces additional benefits in that there is greater satisfaction amongst parents and teachers as this approach leads to lower medication dosages for these children [29,33]. It is well established that ADHD is a multi-factorial disorder, having both psychological and social components, that can have negative outcomes if not diagnosed and managed effectively [1,7,8,26,34-36].

The best clinical outcomes are produced when an integrated biopsychosocial approach is employed for children with ADHD [27,37-39]. The Neuro Emotional Technique (NET), a branch of Chiropractic, was designed to address the biopsychosocial aspects of acute and chronic conditions including non-musculoskeletal conditions [40].

Evidence suggests that 10–30% of children with ADHD who have been prescribed stimulant medications, do not show clinically significant outcomes, and others experience side-effects and need to discontinue their medications [26,31,32,41-43].

The most common side effects of stimulant medications are appetite suppression, weight loss, sleep disturbances, irritability, stomach aches, headaches, rashes, and occasionally the development or aggravation of tics [3,6,26,29,38,41,43,44].

For these children, additional strategies need to be implemented in order to achieve a successful outcome [1,42]. Parents with children diagnosed with ADHD who have had less than satisfactory outcomes with conventional management are presenting to chiropractors looking for alternative interventions. Anecdotally, it has been suggested that ADHD may be managed effectively by NET. There are published case studies on the use of NET for conditions such as hypothyroidism [45], anovulation infertility [46], polycystic ovary syndrome [47], separation anxiety disorder [48], a case series on cancer-related traumatic stress symptoms [49] and a RCT for trigger point sensitivity in chronic neck pain sufferers [50]. However, there is no validation at this time to substantiate the use of NET for children with ADHD. As a result, the application of NET to a cohort of children with medically diagnosed ADHD is being researched. It is important to research an approach being used with a clinic population for which it was not previously designed for nor tested on. The purpose of this paper is to outline the methodology for the RCT employing the CONSORT [51,52] checklist in its design.

### Objectives

The objectives of this research are to:

1. To determine whether the addition of the Neuro Emotional Technique (a new biopsychosocial intervention), to an existing medical regimen can improve clinical outcomes (i.e. reduce inattention, hyperactivity and impulsivity) for children with medically diagnosed ADHD.

2. Furthermore, to determine the responses in the short term (i.e. one month) and medium term (seven months).

## Methods

### Design

Ethics approved, registered, interdisciplinary, placebo controlled, double blind, randomized clinical trial.

### Settings

Four private clinics in Sydney, Australia.

### Care providers

Four chiropractors, three male and one female volunteered their time and services to administer interventions to the participants of the study at no cost. The chiropractors had varied tertiary qualifications: one had Bachelor of Medical Sciences and a Master of Chiropractic; two had a Bachelor of Science and a Master of Chiropractic and one had Bachelor of Science and a Graduate Diploma of Chiropractic. All of the chiropractors had undergone the four NET training workshops over a two year period, and had passed the certification exams in both theory and practice, and a thus were qualified as NET certified practitioners. These practitioners were chosen on the basis that they were experts in the field, were certified and agreed to abide by the study protocols.

### Participants

Parents were initially screened on the phone, and their children were included in the study if inclusion criteria were met. Inclusion criteria comprised: children aged between 5–12 years; children with a medical diagnosis of ADHD for minimum of 2 months, diagnosed by Pediatrician, Psychiatrist or Clinical Psychologist; informed verbal and written consent from parents and participants; children currently undergoing any interventions (pharmacological, psychosocial therapy, educational, occupational therapies etc) or children with the diagnosis of ADHD who have not undergone any treatment; and children who presented with the following comorbid disorders – Conduct Disorder, Oppositional Defiant Disorder, Learning Disabilities, and Anxiety Disorders. Any children who did not meet the inclusion criteria, or who met the exclusion criteria were excluded from the study. Exclusion criteria comprised: A diagnosis of Language difficulties, Mood Disorders (eg. Depressive Disorder or Bipolar Disorder), Communication Disorder, mutism, Pervasive Developmental Disorder (eg. Autism or Asperger's Disorder), Psychosis, profound deafness and other physical or mental disabilities that would prevent participants interacting physically and verbally with the care provider during the consultation; any changes in medications during the course of the study, and any child or parent who had previously undergone any NET treatment.

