### Measures

The Diagnostic and Statistical Manual of Mental Disorders ADHD diagnostic criteria [53,54] were used by the participants' Pediatricians and Clinical Psychologists to establish a diagnosis. The reliable and validated Conners' Parent Rating Scales-Revised Long Version (CPRS-R:L) and Conners' Teacher Rating Scales-Revised Long Version (CTRS-R:L) [55-59] were used pre and post intervention.

The ratings scales were administered pre-intervention to establish baseline data, and were used as outcome assessments to measure the intervention effects at the end of the first month and at the conclusion of the study i.e. in seven months. Of the 14 subscales described in the CPRS-R:L and the 13 subscales described in the CTRS-R:L, two were chosen as primary outcome measures (POMs) and three were chosen as secondary outcome measures (SOMs). Primary outcome measures included Conners' ADHD Index and Conners' Global Index Total subscales H and K respectively. The secondary outcome measures included DSM-IV:Inattentive, DSM-IV:Hyperactive-Impulsive and DSM-IV:Total, subscales L, M, and N respectively.

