### Treatment allocation

Eligible participants were randomly allocated to one of three groups A, B, & C (i.e. group A-sham, group B-treatment, and group C-control). The "QuickCalcs" program from the GraphPad Software [60] was used to randomly sequence 150 numbers (repeated 1×) into the three groups.

Each number and its randomised letter (A, B, or C) were placed in an opaque envelope. Each envelope was numbered consecutively from 1–150.

As each parent called to have their child screened they were allocated the next consecutive number once they were eligible, so that eligible participant no. 1 was allocated to envelope no. 1, etc. The screener was unaware of the sequence of group allocation at the time of screening, hence allocation was concealed at time of recruiting.

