### Protocol

Group A, the sham group, continued with their existing program and the sham protocol was added to their regimen. Group B, the treatment group, continued with their existing program and the NET protocol was added to their regimen. The participants in groups A and B attended a clinical facility for the first month and received eight treatments (two treatments per week) for approximately 15–20 minute sessions. Then, they were scheduled for another six treatments over the next six months (i.e. one treatment per month). Group C, the control group, consisted of children who continued with their existing ADHD treatment regimen as prescribed by their pediatrician, clinical psychologist and/or medical doctor.

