### Analysis

Demographic and baseline characteristics of participant variables will be compared between the three randomised groups using the Restricted Maximum Likelihood (REML) in GenStat 10^th ^Edition [69].

The primary analysis will compare outcomes for each primary and secondary outcome measure between the three groups (treatment, sham and control) using the Restricted Maximum Likelihood (REML) in GenStat 10^th ^Edition [69], to estimate treatment effect with 95% CI. REML is a method for fitting mixed linear models (the models for ANOVA being special cases) which can produce unbiased (or less biased) estimates of variance and covariance parameters. This is a relatively new and powerful technique that allows for data sets that are unbalanced, have missing values, have treatments with unequal variances and/or have correlated error terms [70].

An intention-to-treat (ITT) analysis will be undertaken of the one month and seven month data from the CPRS-R:L and CTRS-R:L for the participants who commenced the study but did not complete.

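### A medication change during the study is an exclusion criterion, so it can only remove children after randomisation, and this is not reconciled with the intention-to-treat analysis

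*Protocol article*

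**What the plan says.** The Participants section puts "any changes in medications during the course of the study" in the list of exclusion criteria and gives the consequence: "Any children who did not meet the inclusion criteria, or who met the exclusion criteria were excluded from the study". Children on medication may enter, since the inclusion criteria admit "children currently undergoing any interventions (pharmacological, psychosocial therapy, educational, occupational therapies etc").

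Under Treatment allocation, parents call for screening and "they were allocated the next consecutive number once they were eligible". Under Measures, the outcome ratings are taken at baseline and then "at the end of the first month and at the conclusion of the study i.e. in seven months".

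The Analysis section states: "An intention-to-treat (ITT) analysis will be undertaken". It applies this to the one-month and seven-month ratings of participants who started but did not finish. It does not mention children whose medication changed.

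Three other statements bear on the point. The Background says of multidisciplinary care that "this approach leads to lower medication dosages for these children", and also that side effects lead some children to stop medication. The Blinding section says that parents of control children knew their allocation. The Recruitment section reports that the last participant completed in March 2008.

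**The concern.** An eligibility criterion can use only what is known before allocation. This one describes an event that happens afterwards, so in practice it is a rule for taking randomised children out of the trial.

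The event is unlikely to be neutral. If added care helps, medication may be lowered. If a child does badly or has side effects, it may be raised, switched or stopped. Control parents know that their child is waiting for treatment, so the rate or direction of change may differ in that arm for reasons other than symptoms. Removing children on such an event selects on something related to outcome, possibly to a different extent in each arm, and the children who remain are no longer a randomised comparison.

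At stake is which children form the primary comparison. The article gives two answers, exclusion under Participants and intention-to-treat under Analysis, and does not say which governs.

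**Working it through.** **Order of events.** Allocation follows directly on eligibility. A change during the study therefore comes after allocation, at any time up to seven months. No child can fail this criterion at screening.

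**The two rules side by side.** If intention-to-treat covers every randomised child, a child with a medication change is analysed, and the exclusion cannot mean removal from the analysis. If the exclusion governs, the analysed set is chosen by a post-randomisation event and the analysis is not intention-to-treat. Fitting the mixed model by REML does not settle the matter. It can use ratings already collected, but there are only two ratings after baseline, and a medication change between them may reflect symptoms that no rating recorded.

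**Size.** The article gives no figure for medication changes, so there is nothing to reproduce. Everything below is an assumed illustration of a simple comparison of the children left after exclusion.

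*Inputs (assumed).* Outcome in SD units, higher is worse: comparator mean 0, NET mean -0.5, SD 1. A latent tendency to a medication change has SD 1 and correlation ρ with outcome within each arm. Its mean is 0 in the comparator and -0.5ρ under NET. A child is removed when this tendency exceeds a common cut c, where c = Φ⁻¹(1 - q) and q is the share of comparators removed.

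*Formulas.*
- Comparator mean after removal: -ρ φ(c)/Φ(c)
- NET mean after removal: -0.5 - ρ φ(c + 0.5ρ)/Φ(c + 0.5ρ)
- Estimated effect: the first minus the second; attenuation: 1 - estimate/0.5

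*Worked case, q = 20%, ρ = 1.* c = 0.8416.
- Comparator: -0.2800/0.80 = -0.350
- NET: the same cut removes 9.0%, so the mean is -0.5 - 0.1622/0.9101 = -0.678
- Estimate: 0.328, attenuation 34%

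*Attenuation over the assumed range.*

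| ρ | q = 10% | 15% | 20% | 25% |
|---|---|---|---|---|
| 1 | 22% | 29% | 34% | 39% |
| 0.8 | 15% | 19% | 23% | 26% |
| 0.5 | 6.3% | 8.1% | 9.5% | 10.7% |
| 0.3 | 2.4% | 3.0% | 3.6% | 4.0% |

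**Direction.** If both arms lose the same share q from the same tail, each mean moves by ρ φ(c)/Φ(c) and the shifts cancel. Unequal shares do not cancel. Take the article's SD of 6.7 (Sample size justification), no true effect, and removal from the worsening tail of 10% under NET against 20-30% of comparators. The false difference is 6.7ρ[φ(c₂)/(1 - q₂) - φ(c₁)/(1 - q₁)], where 1 is NET and 2 the comparator:
- ρ = 0.3, q₂ = 20%: 0.70 - 0.39 = 0.31 points
- ρ = 0.8, q₂ = 30%: 2.66 - 1.05, about 1.6 points

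Both go against NET. Exchanging the two shares reverses the sign, so the documents fix neither size nor direction.

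**The case against.** The strongest reply is that the Analysis section already covers these children. A child taken off study for a medication change has commenced and not completed, which is the group the intention-to-treat sentence names, and nowhere does the article say that such a child's ratings are discarded. This stands. A reader might infer that medication changers are dropped from the primary analysis; the article does not show that. It shows two rules that are not reconciled.

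A reader might also take the 22-39% as the expected loss of effect. That range assumes that removal is fully determined by the final outcome, acts in one tail only and is followed by a complete-case comparison. With weaker correlation the loss is a few percent, and the planned mixed model could use ratings that were kept.

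A third tempting reading is that the rule contradicts the comparator, on the ground that care by the child's own doctor includes adjustments. The Protocol section describes "children who continued with their existing ADHD treatment regimen as prescribed by their pediatrician" and other clinicians. It says nothing of adjustments, and the word for an existing regimen points, if anything, to wanting it stable. That argument is not relied on here.

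The link to the intervention is also indirect. The Background's statement on lower dosages concerns combined pharmacological and psychosocial care, not NET. In the NET-sham contrast, where parents and teachers are described as blinded, knowledge of allocation should not drive differences in medication. It remains true that a real effect, or lack of one, could lead to changes, and that the contrast with the control arm lacks this protection.

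**Conclusion.** The point holds as an error in the stated rule and an unreconciled conflict. The criterion can be met only after randomisation, on an event that may depend on outcome and arm, and excluding children for it is incompatible with analysing all children as randomised. This rests on the text alone.

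Bias in the trial's result is possible but not established. Under the assumed 0.5 SD effect and 10-25% of comparators removed from the worsening tail, attenuation runs from about 2-4% (ρ = 0.3) to 22-39% (ρ = 1). It is about zero when both arms lose the same share from the same tail. The actual rate, direction and balance of medication changes are not given.

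**What to change.** Reconcile the Participants and Analysis sections:

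- Limit the exclusion to information known before randomisation.
- State that every randomised child is analysed in the allocated group in the primary intention-to-treat REML analysis, using all available ratings whatever happens to medication.
- Report by arm the medication changes and any exclusions that resulted from them.
- Give the subset with unchanged medication only as a supportive analysis.

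The Recruitment section shows that follow-up is over, so rewording the criterion can no longer change who was followed. The analysis-population rule, the use of ratings already collected and the by-arm reporting can still be put in place, and cost little more than a written clarification and one table. Ratings that were not collected after an exclusion cannot be recovered, and the report should count them by arm.

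The downside is small: with all children included, medication changes may dilute or mask an effect of NET, which the supportive analysis would help to show. No change to how medication is managed is proposed.

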### Measures

The Diagnostic and Statistical Manual of Mental Disorders ADHD diagnostic criteria [53,54] were used by the participants' Pediatricians and Clinical Psychologists to establish a diagnosis. The reliable and validated Conners' Parent Rating Scales-Revised Long Version (CPRS-R:L) and Conners' Teacher Rating Scales-Revised Long Version (CTRS-R:L) [55-59] were used pre and post intervention.

The ratings scales were administered pre-intervention to establish baseline data, and were used as outcome assessments to measure the intervention effects at the end of the first month and at the conclusion of the study i.e. in seven months. Of the 14 subscales described in the CPRS-R:L and the 13 subscales described in the CTRS-R:L, two were chosen as primary outcome measures (POMs) and three were chosen as secondary outcome measures (SOMs). Primary outcome measures included Conners' ADHD Index and Conners' Global Index Total subscales H and K respectively. The secondary outcome measures included DSM-IV:Inattentive, DSM-IV:Hyperactive-Impulsive and DSM-IV:Total, subscales L, M, and N respectively.

#### Primary Outcome Measures

The Conners' ADHD Index is used to distinguish ADHD children from non-clinical children, and is considered a good screening tool [55,59]. The Conners' Global Index (CGI) is valuable in assessing general psychopathology and for monitoring treatment effectiveness and changes over time. It is sensitive to treatment changes for repeated measures [55,56]. It reflects general behavioral problems, including hyperactivity and attentional difficulties.

#### Secondary Outcome Measures

The DSM-IV:Inattentive subscale was chosen as it has a correlation with the DSM-IV diagnostic criteria for the Inattentive Subtype of ADHD, and focuses on the symptom of inattention. The DSM-IV:Hyperactive-Impulsive subscale was chosen as it has a correlation with the DSM-IV diagnostic criteria for the Hyperactive-Impulsive Subtype of ADHD, and focuses on the symptoms of hyperactivity and impulsivity. The DSM-IV:Total subscale was chosen as it has a correlation with the DSM-IV diagnostic criteria for the Combined Subtype of ADHD, and focuses on all core features of ADHD (i.e. inattention, hyperactivity and impulsivity) [55].

